## Abstract

**Background::**

Knee osteoarthritis (KOA) is a chronic degenerative joint disease commonly occurring in middle-aged and elderly people. The main clinical manifestations are joint pain, limited activity, and decreased muscle strength resulting in decreased motor control ability. Exercise therapy is an effective method to enhance muscle strength of lower limbs, while China's traditional skill Tai Chi (TC) is a combination of activity and inertia, internal and external exercise therapy. In recent years, scholars at home and abroad have found that regular TC can effectively improve patients’ lower limb function and balance ability. The purpose of this study is to explore the effects of TC on lower limb function and balance ability in patients with KOA.

**Methods::**

This is a prospective randomized controlled clinical trial. One hundred forty-six cases of KOA patients will be randomly divided into experimental group and control group according to 1:1 ratio, 73 cases in each group, the control group: sodium hyaluronate; experimental group: TC added on the basis of the control group. Both groups will receive standard treatment for 5 weeks and will be followed up for 3 months. Observation indicators include: the western Ontario and McMaster universities osteoarthritis index; hospital for special surgery knee score; balance stability index, liver and kidney function, adverse reaction rate, etc. SPSS 23.0 software will be used for data analysis.

**Discussion::**

This study will evaluate the effects of TC on lower limb function and balance ability of patients with KOA. The results of this trial will provide a clinical basis for the selection of exercise therapy for patients with KOA.

## Introduction

1

Knee osteoarthritis (KOA) is the most common degenerative joint disease involving cartilage and surrounding tissues, which is characterized by a series of variation such as changes in articular cartilage bone, osteophyte formation, and decreased joint muscle vitality.^[1]^ Clinical manifestations include joint pain, deformity, and reduced function,^[2]^ increasing the risk of fracture and fall.^[3]^ KOA is one of the common causes of mobility disorders and seriously affects the quality of life of patients.^[4,5]^ With the aggravation of population aging, KOA has become a public health problem that endangers global human health.^[6]^ According to statistics, more than 1/3 of the elderly suffer from KOA, and the disability rate is as high as 53%.^[7]^ As for the effective treatment of KOA, a large number of clinical and basic studies have been carried out at home and abroad, mainly including drug therapy, exercise therapy, and surgical treatment,^[8]^ all of which are aimed at relieving pain, delaying disease progression, protecting knee joint, and improving patients’ quality of life. As an important part of non-drug surgical treatment, exercise therapy has been recommended by several clinical guidelines as an effective method for the treatment of KOA.^[9–11]^

Tai Chi (TC), one of the traditional Chinese skills, is a defensive exercise with moderate intensity.^[12]^ It has become one of the most popular forms of exercise, which is rich in content and easy to learn, and is not restricted by space and time. It also emphasizes the integration of essence, qi and spirit combined with breathing to achieve the purpose of cultivating body and mind, preventing and treating diseases when exercising. Studies have found that TC exercise can increase muscle strength, improve balance and sensitivity.^[13]^ In recent years, studies on the effect of TC exercise on lower limb function of KOA patients have increased at home and abroad,^[14–16]^ but its clinical efficacy is still unclear.

Therefore, we intend to evaluate the effects of TC exercise on lower limb function and balance ability in patients with KOA in this randomized controlled trial.

## Methods

2

### Study design

2.1

This is a prospective randomized controlled clinical trial studying the effects of TC on lower limb function and balance in patients with KOA. This protocol follows the latest Consolidated Standards of Reporting Trials (2017) (flowchart is shown in Fig. 1) and Standard Protocol Items: Recommendations for Interventional Trials 2013 statement.

**Figure 1 F1:**
[figure not shown]
Flow diagram.

### Ethics and registration

2.2

This research scheme is in accordance with the Helsinki Declaration and approved by the Clinical Research Ethics Committee of our hospital. This study is registered in the open science framework with registration number of DOI 10.17605/OSF.IO/9WZ6Y. Before being randomly divided into groups, all patients are asked to sign a written informed consent form, and only patients who sign informed consent will be enrolled in the study.

### Patients

2.3

Diagnostic criteria: revised according to the diagnostic criteria for KOA from the American College of Rheumatology^[17]^: ① Patients with knee pain for most of the month; ② Radiographs shows osteophyte formation along the joint margin; ③ Joint fluid examination is consistent with osteoarthritis; ④ Age: ≥40 years old; ⑤ Morning stiffness ≤30 minutes; ⑥ Patients who have bone frictions in joint movement. Those who meet the criteria of ① + ②, ① + ③ + ⑤ + ⑥, or ① + ④ + ⑤ + ⑥ can be diagnosed as KOA.

Inclusion criteria: ① Patients who meet the diagnostic criteria of KOA; ② Age: ≥40 and ≤80 years old; ③ Patients who have certain communication and understanding ability, and can express their own will correctly; ④ Patients who voluntarily accept corresponding treatment and can cooperate; ⑤ Patients who sign the informed consent.

Exclusion criteria: ① Patients who suffer from acute systemic illness; ② Patients who have severe impairment of limb function; ③ Patients who have relative or absolute contraindications of rehabilitation exercise such as blood pressure descent during exercise; ④ Patients combined with hematopoietic system abnormalities; ⑤ Patients combined with severe mental illness; ⑥ Patients who are allergic to sodium hyaluronate; ⑦ Patients who are unable to understand the study protocol or unwilling after explanation.

Elimination criteria: ① Patients with serious adverse events or serious complications, which is not suitable for the next step; ② Patients with poor compliance, affecting the judgment of effectiveness and safety; ③ Patients whose disease progresses during the treatment and need to change treatment plan; ④ Patients who ask to withdraw from the study for any reason.

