### Interventions

2.5

The study will select patients who meet the study criteria by recruiting them at the hospital. A randomized controlled study will be conducted, in which sodium hyaluronate will be used in the control group and the experimental group will include TC exercise on the basis of the control group. Patients in both groups will receive the same routine care, avoid alcohol, tobacco and irritating food, avoid strenuous exercise, and adverse reactions in patients during the test need to be concerned. If necessary, the attending doctor may adjust the treatment according to the patient's condition, and all interventions will be recorded in detail for final outcome analysis. Efficacy assessors are not aware of the study plan, and data statisticians are not involved in study design and implementation. The health of each patient will be assessed before and after the treatment, including observational indicators, and all patients will be followed up by telephone. The follow-up visit includes cardiovascular events and re-hospitalization.

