### Statistical analysis plan

2.9

Use Excel to build database. Full analysis set: including all subjects randomly enrolled, treated and visited at least once, and use full analysis set for intent-to-treat analysis. Per-protocol set: including all subjects who comply with the trial protocol, have no missing baseline variables, and have measurable major variables. Safety set: including subjects randomly enrolled, treated at least once and being safe after at least 1 treatment.

SPSS25.0 statistical analysis software will be used for data analysis in this study. If measurement data meet normal distribution, independent-sample *t* test will be used between groups and paired-sample *t* test will be used within groups; if not, non-parametric test will be used and the results will be expressed in quartiles; Chi-square test will be used for counting data. The incidence of adverse events is compared by chi-square test. When *P* *<* *.05*, the difference is statistically significant.

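### Elimination of randomised patients after treatment starts is not tied to any analysis set, and the set labelled intent-to-treat is not all randomised, so treatment failures may leave the primary denominator

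*Protocol article*

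**What the plan says.** Section 2.3 (Patients) lists four elimination criteria, separate from the exclusion criteria:

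- "Patients with serious adverse events or serious complications, which is not suitable for the next step"
- "Patients with poor compliance, affecting the judgment of effectiveness and safety"
- "Patients whose disease progresses during the treatment and need to change treatment plan"
- "Patients who ask to withdraw from the study for any reason"

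These events arise during treatment, after randomisation. No threshold is given for poor compliance.

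Section 2.9 (Statistical analysis plan) defines the main set: "Full analysis set: including all subjects randomly enrolled, treated and visited at least once, and use full analysis set for intent-to-treat analysis". The per-protocol set is described as "including all subjects who comply with the trial protocol, have no missing baseline variables, and have measurable major variables". Neither definition mentions the elimination criteria.

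The primary endpoint in section 2.6.2 is the total effective rate, a responder proportion divided by the total number of people, with no analysis set named. Section 2.7 places data collection before treatment and at 5 weeks, followed by telephone contact for 3 months. Section 2.4 raises the total from 130 to 146 for about 10% shedding. Section 2.5 lets the attending doctor adjust treatment and says that "all interventions will be recorded in detail for final outcome analysis".

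**The concern.** The endpoint classifies each patient as responder or non-responder. A patient who progresses and needs a changed plan has failed treatment and belongs among the ineffective. If elimination removes that patient from the analysis, the failure disappears from the denominator and the arm's rate rises.

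The loss need not be equal between arms. Both arms receive five weekly injections. The experimental arm also has two Tai Chi sessions a day for 5 weeks, 2 × 7 × 5 = 70 sessions, and so has more opportunity to be judged poorly compliant.

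Unequal removal of non-responders can create an apparent benefit where there is none, or hide a real one. The result would still carry an intent-to-treat label. Because the text leaves the status of eliminated patients open, the denominator could also be settled after the data are seen.

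**Working it through.** **Inputs from the protocol article.** Response rates 91.3% and 68.57%, α = 0.05, 130 patients before shedding and 146 after, 73 per arm (section 2.4); chi-square test (section 2.9). The fractions eliminated are assumptions, since the documents give none. The test is taken as two-sided, which the article does not state.

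**Step 1: the plan's own allowance.** 130 / 0.90 = 144.4, so 145, or 146 for equal arms. The step reproduces. It adds 16 patients (16/146 = 11.0%) on the footing that shed patients do not contribute to the analysis. Nothing below depends on how 130 was obtained.

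**Step 2: effect on the observed rate.** If a fraction e of an arm is eliminated and all of these are non-responders, the observed rate is p / (1 − e).

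- e = 5%: 0.6857 / 0.95 = 72.2%
- e = 10%: 0.6857 / 0.90 = 76.2%

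At e = 10%, the patients removed are 10 / 31.43 = 32% of that arm's non-responders.

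**Step 3: type I error with no true effect.** Both arms 68.57%, 73 per arm, Pearson chi-square, simulated with 400,000 trials per row:

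| Eliminated, Tai Chi arm | Eliminated, control arm | Who is eliminated | Two-sided type I error |
|---|---|---|---|
| 0% | 0% | none | 5.0% |
| 10% | 10% | all non-responders | 5.1% |
| 10% | 0% | half non-responders | 5.9% |
| 10% | 5% | all non-responders | 8.4% |
| 10% | 0% | all non-responders | 16.9% |

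In the last row nearly all false positives favour Tai Chi (16.8 of the 16.9 points). If the control arm loses the 10% instead, the error is again about 17% and favours control.

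**Step 4: power with the planned effect.** With no elimination, simulated power at 73 per arm is 94.7% (normal approximation 93.7%). If 10% of controls are eliminated as progressors, the control rate becomes 76.2%, the difference falls from 22.7 to 91.3 − 76.2 = 15.1 points, and power falls to 69.6%.

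**Step 5: power under the proposed rule.** Counting 10% of each arm as ineffective because the outcome is missing gives 0.913 × 0.90 = 82.2% and 0.6857 × 0.90 = 61.7%. Power at 73 per arm is 79.7% by simulation (79.2% by approximation), close to the planned 80%.

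**The case against.** The strongest reply is that the article never says eliminated patients leave the analysis. The full analysis set does not cite the elimination criteria, and compliance is required only for the per-protocol set. A patient who progresses has been treated and, with weekly injections, may well have been visited, so would meet the full-set definition as written. Section 2.5 also says each patient's health is assessed before and after treatment. This stands: the defect is an unresolved ambiguity, not a declared exclusion. It does not remove the problem. A patient eliminated before week 5 has no efficacy outcome unless assessment continues after elimination, and no passage says that it does, or how such a patient counts.

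Three stronger readings are tempting, and the text does not support them.

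- A reader might infer that section 2.5 keeps patients with adjusted treatment in the analysis and so flatly contradicts section 2.3. It says only that interventions are recorded for the outcome analysis, and an adjustment need not mean progression. The two sections fit poorly and need reconciling.
- A reader might infer that every eliminated patient is a failure. That holds for progression, but not necessarily for poor compliance or for withdrawal for any reason.
- A reader might infer that poor compliance can arise only in the Tai Chi arm. Controls also have injections and lifestyle restrictions; the Tai Chi arm simply has more to comply with.

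The 17% figure is a one-arm, all-non-responder extreme. The planned shedding is not split by arm or by response, so it does not support that scenario in particular.

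Handling of missing outcomes is often left to an analysis plan that is not shown here. The elimination rules and the intent-to-treat definition, however, are stated in this article, and it is those that are fixed badly.

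**Conclusion.** The point holds as a defect in stated rules. Elimination after randomisation, partly on grounds of treatment failure, is not linked to any analysis set, and the set called intent-to-treat is narrower than all randomised patients. On the ordinary reading, supported by the shedding allowance and the single week-5 efficacy assessment, eliminated patients leave the primary denominator.

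Neither the size nor the direction of the bias can be fixed from the documents. Under no true effect, type I error runs from about 5% with equal elimination to about 17% when 10% of one arm, all non-responders, is removed. Under the planned effect, loss of 10% of controls as progressors takes power from about 95% to about 70%. These are illustrations under assumed elimination fractions. They should not be read as a forecast that the trial will produce a false positive.

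The correction should be made before analysis, because it decides who is counted in the primary comparison.

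**What to change.** - In section 2.9, define the primary analysis set as all randomised patients, analysed in the arm to which they were randomised. Name it as the denominator of the total effective rate in section 2.6.2.
- In section 2.3, state that the elimination criteria define only the per-protocol set, and that the week-5 assessment is still sought for these patients unless they withdraw consent.
- Use observed week-5 outcomes where available, including those of poor compliers. Count as ineffective any patient whose treatment plan was changed for progression. As the simple default for a responder endpoint, also count those with a missing week-5 outcome as ineffective.
- Reconcile sections 2.3, 2.5 and 2.9 on data handling. No clinical rule on adjusting or stopping treatment needs to change.
- Multiple imputation is an optional sensitivity analysis.

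The cost is wording plus continued week-5 assessment of eliminated patients. At 10% missing per arm, about 80% power remains with 146 patients, so no extra enrolment is needed.

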### Sample size

2.4

Since the main efficacy index of this study is the total effective rate, the sample size will be estimated according to the total effective rate of pre-experiment. According to the preliminary clinical pre-experiment, the total effective rate of TC combined with sodium hyaluronate was 91.3%, and that of sodium hyaluronate was 68.57%. PASS15.0 will be used for sample size estimation, and an optimal design will be adopted. α = 0.05, β = 0.2, test efficiency = 0.8, the number of experimental group: the number of control group = 1:1, threshold = –0.4. According to the software calculation, the total sample size of the 2 groups will be 130 cases, and 146 cases will be finally included considering the clinical shedding rate of about 10%. The included patients will be numbered according to the order of treatment and divided into the treatment group and the control group by completely random method, with 73 cases in each group.

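### The 130 patients in section 2.4 fit a reversed –0.4 margin test, not the planned chi-square comparison, which needs about 96; at 130 its power is about 91%, not 80%

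*Protocol article*

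**What the plan says.** Section 2.4 (Sample size) of the protocol article bases the trial's size on the primary endpoint, a binary one: "Since the main efficacy index of this study is the total effective rate". The assumed rates come from a pre-experiment: "the total effective rate of TC combined with sodium hyaluronate was 91.3%, and that of sodium hyaluronate was 68.57" per cent. The error rates are given as "α = 0.05, β = 0.2, test efficiency = 0.8", and the allocation and one further input as "1:1, threshold = –0.4". PASS 15.0 is named as the software and an optimal design is mentioned. Neither the test procedure, nor its sidedness, nor the role of the threshold is given. The result is "According to the software calculation, the total sample size of the 2 groups will be 130 cases", raised to 146 (73 per arm) for about 10% loss.

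Section 2.9 (Statistical analysis plan) gives the only test that applies to a rate: "Chi-square test will be used for counting data", with significance at P < .05. It contains no margin. No non-inferiority hypothesis appears anywhere in the article. The introduction and discussion describe an evaluation of the effects of Tai Chi added to sodium hyaluronate.

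**The concern.** A threshold of –0.4 is an input to a margin test, and the plan contains no margin test. If the threshold is left out, the remaining inputs give a number well below 130. If it is used, 130 answers a question that the trial does not ask. Either way, section 2.4 does not support the comparison in section 2.9, and the 80% it states is not the power of that comparison.

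This calculation is the article's only justification for enrolling 146 patients. An ethics committee, a monitoring board or a later reader would take from it the wrong power and the wrong detectable difference, and would find a 40-point margin with no explanation.

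**Working it through.** **Inputs (section 2.4).** pT = 0.913 for Tai Chi plus sodium hyaluronate; pC = 0.6857 for sodium hyaluronate; alpha 0.05; power 0.80; 1:1 allocation; threshold –0.4. Sidedness is not stated, so both are tried.

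**Common terms.**
- Mean rate = (0.913 + 0.6857)/2 = 0.79935.
- Pooled term: A = √(2 × 0.79935 × 0.20065) = √0.32078 = 0.56637.
- Unpooled term: B = √(0.913 × 0.087 + 0.6857 × 0.3143) = √0.29495 = 0.54309.
- Expected difference = 0.913 – 0.6857 = 0.2273.

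**Step 1: reproduce the plan's 130.** Margin test, one-sided 0.05, pooled variance, difference taken as control minus experimental (–0.2273), margin –0.4:

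n = (z0.95 × A + z0.80 × B)² / (–0.2273 + 0.4)²
= (1.6449 × 0.56637 + 0.8416 × 0.54309)² / 0.1727²
= 1.9284 / 0.029825 = 64.66, so 65 per arm and **130 in total**.

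The same set-up gives 124 with unpooled variance and 126 with the Farrington–Manning variance. With the difference taken the other way (experimental minus control, +0.2273), the denominator becomes 0.6273² and n = 4.90, so 5 per arm and 10 in total. At one-sided 0.025 it is 6.24, so 7 per arm.

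**Step 2: what that test asks.** Its null hypothesis is that the control rate is at least 40 points below the Tai Chi rate. Rejecting it shows only that the gap is smaller than 40 points. It would also be rejected if Tai Chi added nothing. The margin is 0.4/0.2273 = 1.76 times the expected benefit.

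**Step 3: the test that section 2.9 plans.** Two-sided 0.05, 80% power, pooled, no margin:

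n = (1.9600 × 0.56637 + 0.8416 × 0.54309)² / 0.2273²
= 2.4560 / 0.051665 = 47.5, so 48 per arm and **96 in total**.

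With continuity correction: n/4 × (1 + √(1 + 4/(n × 0.2273)))² = 55.99, so 56 per arm and 112 in total. Across the variants tried at 80% power, two-sided superiority needs 90 to 112 patients and one-sided 72 to 92. None reaches 130.

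**Step 4: power with 65 evaluable per arm.**
- Normal approximation: Φ[(0.2273 × √65 – 1.9600 × 0.56637)/0.54309] = Φ(1.330) = 90.8%.
- Exact enumeration of the Pearson chi-square: 91.9%.
- Fisher or Yates, exact: 88.3%.

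**Step 5: difference detectable at 80% power with 65 per arm.** Solving the Step 3 formula for pT with pC = 0.6857 gives 0.8856, that is 88.6% against 68.6%, a difference of 20.0 points.

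**Step 6: allowance for loss.** 130/0.9 = 144.4, and 146 × 0.9 = 131.4, so 146 leaves at least 65 per arm if losses are even. This step is sound.

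**The case against.** The strongest reply is that the arithmetic is not wrong. A reader who drops the threshold might infer that the listed inputs do not give 130, or that the figure cannot be reproduced. The documents do not support that: with the threshold included, Step 1 returns 130 exactly, and a sponsor who reruns the software that way could rightly reject the comment. This part of the reply stands, so the point here is a mismatch of hypothesis, not a failed calculation.

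It can also be said that the margin test is a reconstruction. That is true: section 2.4 names no procedure, and agreement in one number is not proof. A one-sided 0.05 superiority test at 95% power also gives 65 per arm (64.46), but it contradicts the stated power of 0.8 and leaves the threshold unused. Steps 3 and 4 do not depend on which procedure was run.

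A reader might further infer that the trial has a non-inferiority criterion under which Tai Chi could be 40 points worse. The documents do not support this either. Section 2.9 has no margin, and in the direction that yields 130 it is the control arm that is allowed to be worse.

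Finally, the trial has more power than it states, so no patient is put at a disadvantage by too small a sample. That stands and lowers the weight of the point. It does not remove it: the article prints a power and a threshold that disagree with its own analysis section, which is more than a detail left out of a condensed article. The mention of an optimal design may be no more than a translation effect, so it calls for clarification only.

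**Conclusion.** The point holds as a mismatch between the sample-size hypothesis and the planned analysis. The only route found from all the listed inputs to 130 is a one-sided 5% margin test with the arms in reverse order. The planned chi-square test needs about 96 patients at 80% power (112 with continuity correction), and with 130 evaluable it has about 91–92% power, or about 88% with Fisher or Yates.

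This rests on the pre-experiment rates of 91.3% and 68.57%, on a two-sided 0.05 reading of section 2.9, and on 65 evaluable patients per arm. It should not be read as a claim that the trial is too small: at its assumed rates it is not under-powered. The weight is should-fix. The stated basis for the trial's size is wrong for its own test, but neither the enrolment nor the analysis has to change.

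**What to change.** Keep 146 patients and rewrite the basis in section 2.4:

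- State that the primary hypothesis is superiority of Tai Chi plus sodium hyaluronate over sodium hyaluronate alone in total effective rate, tested by a two-sided Pearson chi-square at alpha 0.05.
- Replace the power statement, for example: *65 evaluable patients per arm give about 91% power for 91.3% versus 68.57%, or 80% power for a difference of about 20 points (88.6% versus 68.6%); 146 are enrolled to allow for about 10% loss.*
- Remove the –0.4 threshold, which has no counterpart in the analysis.
- Say what the optimal design refers to, or drop the phrase.

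If the sponsor still holds the software output, it should confirm which procedure, sidedness and direction of difference produced 130. The cost is a wording change in one section, with no extra patients and no change to the analysis.
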